### MOSAIC Aims

The primary aims of the trial were:

• to reduce partner violence by 16% among women pregnant and/or with children under five whom GPs or MCH nurses identify as abused or at risk;

• to reduce depression by 16% in women pregnant and/or with children under five whom GPs or MCH nurses identify as abused or at risk; and

• to strengthen the general health and wellbeing and mother-child bonding of abused or at-risk women.

The secondary aims were:

• to strengthen infrastructure support for primary care management of partner violence, by enhancing effective inter-sectoral collaboration between general practice and community-based family violence networks; and

• to enhance primary care case management of family members living with partner violence.

The major hypothesis tested in MOSAIC was that mentor mother support would reduce both partner abuse and depression and the hypothesised pathway for this to occur was the following:

• that by reducing isolation, providing links to community resources and using strength-based support, sustained help from mentor mothers to women who are pregnant and/or have children under five referred by their primary care provider will encourage women to take actions to increase their safety; and

• that any reduction of abuse, together with continued non-professional mentor support, will reduce the level of depression and enhance women's general health and mother-child bonding.

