### Sample size considerations

With 80% power and 95% confidence, MOSAIC aimed to detect a difference of 16% in abuse or depression a year after recruitment. This was originally estimated to require 165 women in each trial arm with individual randomisation. This reduction was thought to be attainable from a level of any prevalence value for either IPV or depression between 30% and 70% in the control group of women already identified by their GPs as abused or at risk. With cluster randomisation, assuming an intra-class correlation of 0.02 (previously found in a GP partner violence study [18]), the sample size required increased to 190 in each arm. Given the mobility of this vulnerable, sometimes fearful population an expected attrition and loss to follow up of as much as 45% could be expected, requiring 350 to be recruited in each arm. Piloting data indicated that 40 weeks would be required for referral and recruitment of this required number of participants.

By May 2007 (well beyond the 40 week period), both referral and recruitment had been slower than expected and the ratio of intervention to comparison for both those referred and recruited was approximately 2:1. At this stage 131 women in the intervention arm and 71 women in the comparison arm had been referred and of these 63% had been recruited. It was decided to extend the recruitment period for another 7 months, and include one additional MCH nurse team in each arm of the trial.

The estimated sample size was recalculated and we then estimated that, for simple random sampling, with 118 in the intervention arm and 64 in the comparison arm, the study would have 80% power and 95% confidence of being able to detect a difference between arms of 22% for IPV, 18% for depression and two units in the mental component score (MCS) of the SF36. Allowing for the overall 37% attrition rate seen to that time and the 10% inflation factor for the cluster sampling, we hoped to achieve total referrals of 206 women (+75) in the intervention arm and 112 (+41) in the comparison arm to be referred in the extra time period.

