***Years Australian residency***				
Australian	76	***67***	37	***62***
Less than five years	9	***8***	7	***12***
5–14 yrs	9	***8***	9	***15***
14–43 yrs	16	***14***	6	***10***
Missing	4	***4***	1	***2***

**Table 2 T2:** Comparison of abuse and depression status by arm

	**Intervention, n = 114**		**Comparison, n = 60**	
**IPV status**	n	%	n	%
0	9	*8*	6	*10*
3–6	11	*10*	2	*3*
**≥ 7**	93	***82***	48	***80***
Missing	1	*1*	4	*7*
				

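### The recalculated sample size spends its attrition allowance on women who were referred but not recruited, and allows nothing for loss before the 12-month outcome

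*Protocol article*

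**What the plan says.** All the sample-size figures are in the protocol article under Sample size considerations.

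- **First calculation.** The target was a 16-point difference at one year. It needed 165 women per arm, raised to 190 for clustering. Then "an expected attrition and loss to follow up of as much as 45% could be expected, requiring 350 to be recruited in each arm". This allowance applies to recruited women.
- **Position in May 2007.** "131 women in the intervention arm and 71 women in the comparison arm had been referred and of these 63% had been recruited".
- **Recalculation.** "for simple random sampling, with 118 in the intervention arm and 64 in the comparison arm", it is said that "the study would have 80% power and 95% confidence of being able to detect a difference between arms of 22% for IPV, 18% for depression". The referral targets of 206 (75 more) and 112 (41 more) follow after "Allowing for the overall 37% attrition rate seen to that time and the 10% inflation factor for the cluster sampling".

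Data collection places the outcome survey twelve months after baseline. MOSAIC Aims still reads "to reduce partner violence by 16% among women pregnant and/or with children under five", with the same 16% for depression. Table 2 gives the numbers recruited: "Intervention, n = 114", and 60 in the comparison arm.

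**The concern.** The word attrition covers two different losses. In the first calculation it is loss after recruitment. In the recalculation it is 37%, the exact complement of the 63% of referred women who had been recruited. A woman who is referred but never recruited is lost before baseline. A woman who is recruited but not surveyed at 12 months is lost later, and the power depends on that second loss too.

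If the 37% is only the earlier loss, the 118 and 64 are effective numbers at baseline and the 80% power assumes that every recruited woman supplies an outcome. A non-significant result would then be read against a power statement that is too favourable. The population matters here, because the same section expects heavy loss from mobile and sometimes fearful women.

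**Working it through.** **1. Reproduce the targets.** Inputs from Sample size considerations: 118 and 64 before inflation, cluster factor 1.10, recruited share 0.63.

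- Intervention: 118 × 1.10 / 0.63 = 206.0 (stated 206)
- Comparison: 64 × 1.10 / 0.63 = 111.7 (stated 112)
- Increments: 206 − 131 = 75 and 112 − 71 = 41, as stated. The targets are therefore in the same unit, referrals, to which the 63% applies.

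Multiplying up instead of dividing (118 × 1.10 × 1.37 = 178; 64 × 1.10 × 1.37 = 96) does not match.

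**2. See what is left for follow-up loss.** 206 × 0.63 = 130 and 112 × 0.63 = 71 recruited women. These equal 118 × 1.10 and 64 × 1.10, so nothing is left. The first calculation did have the factor: 190 / 0.55 = 345, stated as 350.

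**3. Power for 22 points.** Two-proportion test, pooled variance under the null, two-sided 5%:

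power = Φ[(d − 1.96·se₀)/se₁], with se₀ = √[p̄(1 − p̄)(1/n₁ + 1/n₂)] and se₁ = √[p₁(1 − p₁)/n₁ + p₂(1 − p₂)/n₂].

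Example at control rate 60% and intervention rate 38%, so p̄ = 0.457:

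- No loss, 118/64: se₀ = 0.0773, se₁ = 0.0758, (0.22 − 0.1516)/0.0758 = 0.90, power 82%
- 45% loss, 64.9/35.2: se₀ = 0.1043, se₁ = 0.1022, (0.22 − 0.2044)/0.1022 = 0.15, power 56%

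The recalculation states no control rate. The 30–70% range is the one given for the first calculation. The 45% loss is the article's own upper figure; the 20% is an assumption.

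Power with 118/64 effective women:

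| 12-month loss | Control 30% | 40% | 50% | 60% | 70% |
|---|---|---|---|---|---|
| 0% | 96% | 89% | 84% | 82% | 83% |
| 20% | 92% | 82% | 75% | 72% | 73% |
| 45% | 80% | 67% | 59% | 56% | 57% |

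Power falls below 80% once loss exceeds about 10%, 4% and 6% at control rates of 50%, 60% and 70%. At 40% the limit is about 23%, and at 30% about 45%.

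**4. The same with the women recruited.** Effective numbers = 114 or 60 × retention / 1.10:

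| 12-month loss | Effective numbers | Power for 22 points, control 30–70% | Difference detectable at 80% power |
|---|---|---|---|
| 0% | 104/55 | 76–93% | 19–23 points |
| 20% | 83/44 | 66–88% | 20–26 points |
| 45% | 57/30 | 50–74% | 23–31 points |

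**5. The other stated differences, 118/64 with no loss.** At control rates of 50–70%, power is 54–56% for 16 points and 64–66% for 18 points. At 30% it is 73% and 83%. These gaps are present before any follow-up loss is considered.

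**The case against.** The strongest objection is to size and attribution; the arithmetic of the 37% is not in doubt.

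- **The shortfall depends on the control rate.** A reader might infer that the 80% power for 22 points is simply absent. The documents do not support that. At 30%, 118/64 keeps about 80% power even at 45% loss, and 114/60 with 20% loss has 88%. This stands, so the result must be shown over the range.
- **Missed recruitment is a separate cause.** With 114/60 and no loss at all, power at control rates of 50–70% is already 76–78%. The referral targets were stated as a hope, and the Discussion reports the low referrals openly. Missing a target is not an arithmetic error. This stands.
- **The 16% and 18% gaps are not caused by the attrition error.** A reader might link them to it. At control rates of 50–70%, 118/64 falls short for both before any loss, and the article openly moved from 16 to larger differences. This stands.
- **A non-significant result does not always leave 16 points open.** With 57/30 effective women and rates near 50%, the 95% interval extends about 1.96 × √(0.25/57 + 0.25/30) = 22 points either side. A difference of 10 points in the unfavourable direction would be non-significant, yet its favourable limit is about 12 points, which excludes 16.
- **The 37% might already include 12-month loss.** This does not stand. It equals the stated non-recruitment exactly, and the targets contain no second factor.

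The primary outcomes also include mean depression and parenting-stress scores, which these two-proportion figures do not cover.

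**Conclusion.** The point holds. The recalculation relabels non-recruitment as attrition and drops the allowance for loss after recruitment that the same section had earlier put at up to 45%. At control rates of 50–70%, the stated 80% power for 22 points survives only about 4–10% loss. With 118/64 effective women it falls to 72–75% at 20% loss and 56–59% at 45%. At a 30% control rate it is about 80% even at 45% loss.

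For the 114/60 women recruited, the realistic statement is a range: 66–88% at 20% loss and 50–74% at 45%, over control rates of 30–70%. These figures combine the missing allowance with the recruitment shortfall. They rest on a design effect of 1.10, a pooled two-sided 5% test, and loss rates that are either assumed (20%) or the article's upper figure (45%).

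The mismatch with the 16% aim is real but separate. The error concerns what the trial is said to be able to detect. It does not change the analysis or any estimate.

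**What to change.** In Sample size considerations:

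1. Relabel the 37% as non-recruitment of referred women, and say that the recalculation allowed for no loss before 12 months.
2. Restate power and detectable differences from 114/60 × 12-month retention / design effect. Use observed retention once known; until then show a range up to the 45% loss already cited. State the assumed control rate and show the results over its range, for IPV and for depression.

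In MOSAIC Aims, keep the 16% on record as the original aim. Note beside it that the trial as revised does not have 80% power for a difference of that size. In reporting, let the confidence interval decide whether 16 points is excluded, rather than presuming the answer from significance or its absence.

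The cost is one recalculation and some wording. The stated power becomes less favourable, and no extra women are needed.

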### Recruitment of the clusters: GP practices and maternal and child health teams

Prior to study commencement, support for MOSAIC was obtained from the five General Practice Divisions in the planned catchment area for the study, and permission granted to contact GP practices in the region. General practitioners (GPs) were invited from practices included in the Maternity Affiliate Shared Care List for the Victorian Department of Human Services North West Region, and GPs who were members of the five participating Divisions of General Practice (including all Vietnamese GPs in the region) were also sent letters of invitation. Vietnamese GPs were approached in person by a Vietnamese project officer and invited to participate. MCH nurse teams located in six local government areas in North West Melbourne were informed about MOSAIC and invited to participate.

Formal written invitations included information about: the rationale and design of MOSAIC; the requirement for participation in six hours of professional development addressing IPV identification and management; a commitment to invite and refer women to the study for a required period of time; acceptance of the process of randomisation; a copy of the Memorandum of Understanding regarding participation; and contact details for further information about the trial.

24 GP practices (27 GPs) and six (later increased to eight) MCH teams agreed to participate by returning a signed copy of the Memorandum of Understanding.

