#### ◦ Process and impact evaluation

Multiple methods have been used to evaluate the study's processes during implementation and following the completion of the study [47]. One year into the two year referral period, we conducted telephone interviews with (74/91 81%) MCH nurses and (13/27, 48%) GPs to assess their views of their training and support in order to respond with further strategies to encourage enhanced identification and referral of women. After the referral period was complete, surveys of participating MCH nurses and GPs sought their views on the impact of MOSAIC on their practice and the nature of the intervention. In-depth interviews with 30% of mentored women (n = 36 including 11 Vietnamese women) and 26% of mentors (n = 18 including 4 Vietnamese mentors) explored their overall experiences of mentoring and being mentored.

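### At ICC 0.02, the 10% cluster allowance behind the 206/112 referral targets is enough only if the 32 clusters are nearly equal in size, and it is probably too small

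*Protocol article*

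**What the plan says.** Under *Sample size considerations*, the protocol article gives two calculations.

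- **Initial:** 165 women per arm under individual randomisation. Then, "assuming an intra-class correlation of 0.02", "the sample size required increased to 190 in each arm".
- **Recalculation after slow recruitment:** "for simple random sampling, with 118 in the intervention arm and 64 in the comparison arm", the study would have 80% power for "a difference between arms of 22% for IPV, 18% for depression". The targets of 206 and 112 referrals follow after allowing for 37% attrition and "the 10% inflation factor for the cluster sampling". No ICC or cluster size is given for this step.

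The clusters are described under *Recruitment of the clusters*: "24 GP practices (27 GPs) and six (later increased to eight) MCH teams agreed to participate". The number of nurses appears under *Process and impact evaluation*, where interviews were held with ("74/91 81%) MCH nurses and (13/27, 48%) GPs". *Randomisation* adds that nurse teams were stratified by births in the local government area.

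**The concern.** A design effect computed from the plain average cluster size is correct only when clusters are equal. When they vary, the size-weighted average applies, and that is always larger. Here there is about 1.1 participating GP per practice (27/24) against roughly 11 to 15 nurses per team (91/8 to 91/6). Teams also serve areas with different numbers of births, and two of them joined only for the extension. A factor that matches the plain average leaves no margin for this.

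The 206/112 targets exist to deliver, under clustering, what 118 and 64 women would deliver under simple random sampling. If the factor is too small, meeting the targets gives less than 80% power for 22 and 18 points. A reader of a null result would then credit the trial with more sensitivity than it had.

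**Working it through.** **Inputs from the article:** 118 and 64 women (182 in total); 10% inflation; 37% attrition; ICC 0.02 (stated for the initial calculation only); 24 practices with 27 GPs; eight teams; 91 nurses; "With 80% power and 95% confidence", taken as two-sided 5%.

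**Assumptions:** ICC 0.02 also applies to the recalculation. The share of women referred by nurse teams is not reported, so it is varied. Within each type, clusters are taken as equal in size, which is favourable to the plan.

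**1. Reproduce the targets.** 118 × 1.10 / 0.63 = 206.0 and 64 × 1.10 / 0.63 = 111.7. Both match, so 1.10 is the factor used.

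**2. What 10% implies.** With equal clusters the design effect is DE = 1 + ICC × (m − 1). Setting 1.10 = 1 + 0.02 × (m − 1) gives m = 6.0. The plain average over 32 clusters is 182/32 = 5.7 (DE 1.094) or, after the 10% inflation, 200/32 = 6.25 (DE 1.105). The factor therefore matches the equal-cluster case almost exactly.

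**3. Room for inequality.** With unequal clusters, DE = 1 + ICC × (Σm²/Σm − 1), and Σm²/Σm equals mean size × (1 + CV²).
- With 182 women, DE ≤ 1.10 needs 5.69 × (1 + CV²) ≤ 6.0, so CV² ≤ 0.055 and CV ≤ 0.23.
- With 200 women, 10% is already marginally short when all clusters are equal.
- In terms of the team share s with 182 women: 182 × [s²/8 + (1 − s)²/24] = 6 gives s ≈ 0.15 or 0.35. The allowance is therefore enough only if teams refer between about 15% and 35% of the women.

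**4. Consequences by team share.** Power after the allowance is Φ(2.802 × √(1.10/DE) − 1.960). This takes the simple-random-sampling power as exactly 80%, because the control rates behind 22 and 18 points are not given. Detectable differences scale by √(DE/1.10). Each range runs from 182 to 200 women.

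| Share from teams | Women per team / practice | DE | Power | 22 points becomes | 18 points becomes |
|---|---|---|---|---|---|
| 25% (all clusters equal) | 5.7–6.25 / 5.7–6.25 | 1.09–1.105 | about 80% | 21.9–22.0 | 17.9–18.0 |
| 50% | 11.4–12.5 / 3.8–4.2 | 1.13–1.15 | 78–79% | 22.3–22.5 | 18.3–18.4 |
| 77% (91 of 118 clinicians) | 17.5–19.3 / 1.7–1.9 | 1.26–1.29 | 74–75% | 23.5–23.8 | 19.3–19.5 |
| 100% | 22.8–25.0 / 0 | 1.44–1.48 | 68–69% | 25.1–25.5 | 20.6–20.9 |

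Worked line for 77% and 182 women: Σm²/Σm = 0.771 × 17.54 + 0.229 × 1.74 = 13.9, so DE = 1 + 0.02 × 12.9 = 1.26. Keeping the plan's logic at this share would need 118 × 1.26 / 0.63 ≈ 236 and 64 × 1.26 / 0.63 ≈ 128 referrals (241 and 131 with 200 women).

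**5. Sensitivity to the ICC at the 77% share.** ICC 0.01 gives DE 1.13–1.14 and power of about 79%. ICC 0.05 gives power of 61–63%. The 10% would be just enough at ICC 0.10/12.9 ≈ 0.008.

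**The case against.** A reader might infer that the recalculated 80% power and the 22- and 18-point differences are themselves wrong because they rest on the 10%. The article does not support that. They are stated for simple random sampling, and the 10% enters afterwards and affects only the referral targets. Nor is there an arithmetic slip, since 206 and 112 reproduce.

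A reader might also infer that a shortfall is established. It is not. Women per cluster and the split between nurses and GPs are unreported. The 77% share assumes that every clinician refers equally, which nothing in the article tests, and GP practices were piloted as a referral source. If teams referred half the women, the loss is only one to two points. The recalculation states no ICC, and a value near 0.008 would make 10% sufficient even at the 77% share.

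Average cluster size is a common planning simplification, and a condensed article may leave the derivation of a factor to the full protocol. Recruitment has closed with 114 and 60 women (Table 1), and the planned analysis adjusts for practice or team, so the confidence intervals will show the precision actually achieved.

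All of this limits the size and certainty of the point but does not remove it. The article commits to a specific factor and derives targets from it. At its own ICC that factor leaves almost no room for the unequal clusters it describes. Adjusting the analysis for clustering protects its validity but does not restore planned power.

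**Conclusion.** The point holds in conditional form. At ICC 0.02, the 10% allowance is adequate only for 32 nearly equal clusters of about six women. With eight teams holding 91 nurses beside 24 practices holding 27 GPs, it is probably too small. What is in doubt is whether the inflated targets deliver the stated power and differences under clustering.

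The loss is one to two points of power if teams refer half the women, about five to six if referral follows clinician numbers, and about 11 to 12 if teams refer everyone. These figures rest on carrying ICC 0.02 over to the recalculation and on equal sizes within each cluster type. Variation among teams would add to the loss, and a smaller ICC would reduce it. The consequence is for how a null result is read; the planned analysis is unaffected.

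**What to change.** State the ICC used in the recalculation. Count the women per practice and per team, compute the design effect as 1 + ICC × (Σm²/Σm − 1), and use it in place of the flat 10%. Restate the detectable differences for IPV and depression after clustering, for the numbers actually enrolled, with a short sensitivity range for the ICC. No further enrolment and no change to the analysis is needed.

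The cost is one recalculation from counts the trial should already hold, and a stated precision that will probably be somewhat less favourable.

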### Data collection

Baseline data were collected on recruitment and outcome evaluation data were collected twelve months later. We repeated the two primary outcome measures after twelve months of mentoring in the few instances where there was a delay of three months or more in a participant being allocated a mentor. Any woman who was offered a mentor received a supplementary questionnaire about her experience of mentoring.

#### ◦ Outcome evaluation

Abuse status was measured using the Composite Abuse Scale (CAS), a comprehensive, well-tested and validated screening tool which discriminates between differing forms of abuse (severe combined abuse, physical abuse only, emotional abuse and harassment) [42]. Depression was measured using the Edinburgh Postnatal Depression Scale (EPDS) [43], which has been validated with mothers (and fathers) outside the immediate postpartum period [44,45]. Women's general health status was measured using the SF36 [36]. The mother-child relationship was measured using the Parenting Stress Index (PSI) Short Form, which can be used for parents of children as young as one month [46] and has been used previously with women experiencing abuse. The PSI Short Form (SF), has three subscales derived from and well validated against the long form: – Parental Distress, Parent-Child Dysfunctional Interaction (P-CDI) and Difficult Child. The P-CDI subscale elicits threat to the parent-child relationship [46]. Use of and satisfaction with GP and MCH nurse care was measured via participant self-report.

#### ◦ Process and impact evaluation

Multiple methods have been used to evaluate the study's processes during implementation and following the completion of the study [47]. One year into the two year referral period, we conducted telephone interviews with (74/91 81%) MCH nurses and (13/27, 48%) GPs to assess their views of their training and support in order to respond with further strategies to encourage enhanced identification and referral of women. After the referral period was complete, surveys of participating MCH nurses and GPs sought their views on the impact of MOSAIC on their practice and the nature of the intervention. In-depth interviews with 30% of mentored women (n = 36 including 11 Vietnamese women) and 26% of mentors (n = 18 including 4 Vietnamese mentors) explored their overall experiences of mentoring and being mentored.

